## IX -1- 7- Tolerance

Adverse events

Adverse events will be described per treatment group according to their MedDRA codes (SOC and PT) and according to their intensity and imputability to the treatment. The proportion of subjects with at least one adverse event will be compared between the groups using the Chi-squared test or Fisher’s exact test.

## IX -2 - STATISTICAL CRITERIA FOR TERMINATING THE RESEARCH

None

## IX -3 - METHOD FOR TAKING INTO ACCOUNT MISSING, UNUSED AND INVALID DATA

In the event of missing data regarding the primary endpoint, the method of maximum bias will be used so as not to favour the hypotheses to be tested. The missing values in the group to be tested will be replaced by failures, while in the reference group, they will be replaced by successful cases, and vice versa.

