## IV - 3 - REQUIRED NUMBER OF SUBJECTS

The return-to-work rate at 1 year is estimated to be 70% in the control group. The hypothesis is to reach 80% in the intervention group. With a 5% risk and a power of 80%, a total of 600 patients are planned to be enrolled: 300 patients in the short spa therapy group and 300 patients in the control group. Taking into account the risk of loss-to-follow-up, 700 patients will be enrolled.

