## IX -1- 5- Primary endpoint analysis

An intention-to-treat analysis will be carried out, i.e., all patients randomised will be analysed in their randomisation arm, regardless of the treatment received and any missing information. The bilateral tests will be carried out at the 5% threshold. The return-to-work rate percentage will be compared using the Chi-squared test.

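### The maximum-bias rule for missing return-to-work data is not reflected in the sample size, and above 9.1% missing it reverses the hypothesised effect

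*Protocol*

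**What the plan says.** Section IV-3 sets the planning rates: "The return-to-work rate at 1 year is estimated to be 70% in the control group" and "The hypothesis is to reach 80% in the intervention group". It continues: "With a 5% risk and a power of 80%, a total of 600 patients are planned to be enrolled", which is 300 per arm. The total is then raised: "Taking into account the risk of loss-to-follow-up, 700 patients will be enrolled". No loss rate is printed. The Summary splits the 700 into 350 per arm.

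Section IX-1-5 defines the primary analysis. Under intention to treat, "all patients randomised will be analysed in their randomisation arm, regardless of the treatment received and any missing information". The test is two-sided ("The bilateral tests will be carried out at the 5% threshold") and is a comparison of proportions: "The return-to-work rate percentage will be compared using the Chi-squared test".

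Section IX-3 states how a missing primary endpoint is handled. It names the method of maximum bias and gives its purpose as not favouring the hypotheses under test. Missing "values in the group to be tested will be replaced by failures, while in the reference group, they will be replaced by successful cases". The sentence closes by adding the reverse, with no explanation. The protocol gives no other method for the primary endpoint and does not call this one a sensitivity analysis.

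**The concern.** Read together, IX-1-5 and IX-3 score every missing spa patient as not back at work and every missing control patient as back at work, and put all of them in the primary test. The sample size does not allow for this. Adding 100 patients to replace losses works only if those lost are left out, so that 300 observed patients per arm are compared. Under IX-3 each lost patient stays in and counts against the intervention, so power depends on the amount of missing data.

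Two things are at stake. A treatment exactly as good as hypothesised could look neutral or harmful. And if the closing words of IX-3 mean that the opposite imputation is also run, the trial has two primary results that may point in opposite directions, with no rule for which one counts. Neither is an estimate of the treatment effect; each is an extreme bound.

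**Working it through.** **Inputs.** Control rate 0.70, spa rate 0.80, two-sided 5%, 80% power, 300 evaluable per arm (IV-3, IX-1-5); 350 randomised per arm (Summary). The missing proportion *m* per arm is not printed. The step from 600 to 700 implies 100/700 = 14.3%, or 50 per arm if losses are equal and each lost patient lacks the 12-month outcome. That is an assumption, so a range is shown.

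**1. The plan's own figure.** With pooled variance,

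n = [1.960 × √(2 × 0.75 × 0.25) + 0.842 × √(0.21 + 0.16)]² / 0.10² = (1.200 + 0.512)² / 0.01 ≈ 293.2, so 294 per arm.

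The protocol's 300 per arm agrees, with power 80.9%. The inflation also agrees: 600 / (1 − 100/700) = 700.

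**2. Rates after imputation under IX-3.**

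- Spa: 0.80(1 − m)
- Control: 0.70(1 − m) + m
- Difference: 0.10 − 1.10m

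The difference is zero at m = 0.10/1.10 = 9.1%, about 32 patients per arm, and negative beyond that.

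**3. Power to show benefit, 350 per arm.** The formula is Φ{(d − 1.960 × SE₀)/SE₁}, where d is the signed difference from step 2, SE₀ the pooled and SE₁ the unpooled standard error. Only results favouring spa count.

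| Missing per arm | Spa | Control | Difference (points) | Power for spa | Significant for control |
|---|---|---|---|---|---|
| 0% | 80.0% | 70.0% | +10.0 | 86.5% | 0% |
| 1% | 79.2% | 70.3% | +8.9 | 77.5% | 0% |
| 2% | 78.4% | 70.6% | +7.8 | 65.9% | <0.01% |
| 3% | 77.6% | 70.9% | +6.7 | 52.7% | <0.01% |
| 5% | 76.0% | 71.5% | +4.5 | 27.2% | 0.05% |
| 8% | 73.6% | 72.4% | +1.2 | 5.5% | 1.0% |
| 9.1% | 72.7% | 72.7% | 0 | 2.5% | 2.5% |
| 14.3% | 68.6% | 74.3% | −5.7 | 0.01% | 38.7% |

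In counts, the last row is 300 × 0.80 = 240 of 350 for spa and 300 × 0.70 + 50 = 260 of 350 for control.

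**4. Simulation check with the Pearson chi-squared test.** With the number missing held fixed, power is 86.6% at 0%, 66.3% at 2%, 24.5% at 5% and 1.5% at 9.1%. At 14.3% it is 0.002%, with 37.3% significant for control. Letting the number missing vary by chance at 14.3% gives 0.016% and 38.8%. The small gaps from the table arise because a fixed number missing leaves less sampling variation than the formula assumes.

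**5. Other ways of handling the same 50 missing per arm.** Comparing the 300 + 300 observed patients gives 81% power, which is what IV-3 relies on. Counting missing as failure in both arms gives 66% to 69%. Under IX-3, the true spa rate would have to be about 97% for 80% power.

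**6. The converse imputation.** With missing spa patients as successes and missing control patients as failures, 50 missing per arm and true rates of 70% and 80%, the imputed rates are 290/350 = 82.9% and 210/350 = 60.0%, and power is essentially 100%. With no true effect (70% in both arms) they are 260/350 = 74.3% and 210/350 = 60.0%. Spa is then declared superior in 98.2% of trials by the formula and 98.8% by simulation.

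**The case against.** The best case for the plan has four parts.

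First, the 14.3% is inferred. The protocol prints no rate, and it plans post, email, telephone reminders, help with questionnaires and a gift voucher to keep missing data low. This stands: the near-zero power figure is conditional, which is why the range is given. It does not rescue the rule. Power falls below 80% at 1% missing (3.5 patients per arm), and section I-4 itself lists follow-up among the main difficulties.

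Second, a deliberately conservative rule is a recognisable choice in an open trial whose endpoint the protocol calls partly subjective. In its stated direction it does not inflate false claims of benefit. That is true, but it protects against one error by making the opposite one likely: at 14.3% missing, a treatment that works as hypothesised has a 37% to 39% chance of appearing significantly worse. Intention to treat requires patients to stay in their arm; it does not require opposite outcomes to be assigned by arm.

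Third, the closing words of IX-3 may be loose drafting, or may describe a pair of bounds. Given the stated purpose, the favourable direction could hardly be meant to establish efficacy. This also stands: the false-positive figure of about 98% to 99% applies only if that direction is allowed to decide. The text does not exclude this, and the loss of power does not depend on it.

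Fourth, enrolling extra patients and imputing conservatively are not logically incompatible. Agreed; the defect is that the sample size ignores what the imputation does to the effect. It is not a matter left to the statistical analysis plan, because the protocol itself fixes the rule.

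**Conclusion.** The concern holds and must be fixed. The only rule the protocol gives for a missing primary endpoint subtracts 1.1 percentage points from the expected difference for every 1% missing per arm, and the sample size takes no account of it. The stated 80% power survives only if less than about 1% of outcomes are missing. It is about 66% at 2% missing and 25% to 27% at 5%, and the expected effect reverses above 9.1%. At the implied 14.3%, power is about 0.01%.

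These figures assume the planning rates of 70% and 80%, 350 per arm, equal missingness in both arms, and missingness unrelated to outcome. The 14.3% further assumes that the whole increase from 600 to 700 covers missing primary outcomes. The conclusion does not rest on that last assumption. The status of the converse imputation is unclear as written and also needs resolving.

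**What to change.** Rewrite IX-3 so that the primary analysis uses multiple imputation under missing-at-random, done within arm. The imputation model can use data the protocol already collects: site, duration of sick leave at enrolment, baseline scores, and work status and sick-leave days at Months 3 and 6. Keep the maximum-bias imputation as a labelled sensitivity analysis, with both directions defined explicitly and a tipping-point display showing how unequal the outcomes of missing patients would have to be to change the conclusion. Neither extreme should decide the primary result. State in IV-3 the loss rate behind the increase from 600 to 700.

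If a simpler single rule is preferred, counting missing as failure in both arms avoids the reversal, but its 66% to 69% power at 14.3% missing would have to be reflected in the sample size.

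The cost is one paragraph in IX-3, a sentence in IV-3 and some analysis work; visits, data collection and patient care do not change. The downside is reliance on missing-at-random, which is weakest for patients lost before Month 3, who supply only baseline data. The retained bounds and tipping-point display test that assumption. The change should be made before unblinding, because the choice between these analyses could determine the trial's conclusion.

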## IX - 4- CHOICE OF INDIVIDUALS TO BE INCLUDED IN THE ANALYSES

Adults (between the ages of 18 and 60), either male or female, with isolated or lower back pain or back and radicular pain after classification of the disease, on sick leave from 4 to 24 weeks, and who meet the inclusion criteria of the study.

## IX - 5 - DESCRIPTION OF PROTOCOL DEVIATIONS

The blind review of the data will include the list of individual data as well as the list of deviations, providing the level of deviation for each subject (“no deviation”, “minor deviation” or “major deviation”). A descriptive analysis of protocol deviations will be presented by product group.

# X – SAFETY ASSESSMENT

## X - 1 - DESCRIPTION OF THE SAFETY ASSESSMENT PARAMETERS

**Adverse event**

Any harmful manifestation occurring in an individual taking part in a biomedical research study, regardless of whether or not the manifestation is related to the research.

**Adverse event in a research study not involving a product mentioned in Article L. 5311-1** (medicinal products, biomaterials and medical devices, in vitro diagnostic medical devices, labile blood products, organs, tissues, cells and products of human or animal origin, and cellular products for therapeutic purposes).

Any adverse event due to the research.

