## VII - 3 - FOLLOW-UP VISITS after the intervention

Patients will undergo follow-up at Months 3, 6 and 12. Follow-up will be done by post or email, depending on the patient’s preference, together with a telephone call if no response is received.

The following data will be evaluated:

- Professional status and return to work;
- Periods of sick leave since the previous visit (dates and number of days of sick leave);
- Assessment of pain over the past 48 hours, assessed using a numeric scale from 0 to 100;
- Lower back pain progress;
- Treatment since the previous visit;
- Adverse events collected;
- Functional indices: Quebec scale;
- Anxiety/Depression: HAD questionnaire;
- Quality of Life: MOS SF-12 questionnaire;
- Fear-avoidance beliefs: FABQ questionnaire (only at the Month 12 assessment);
- Coping strategies: CSQ questionnaire (only at the Month 12 assessment);
- Treatment satisfaction (only at the Month 12 assessment).

Pain over the past 48 hours will also be systematically evaluated once every fortnight by phone (using a numeric scale from 0 to 100). VOICE RESPONSE SYSTEM

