**Serious adverse event or effect**

Any adverse event or effect that leads to death, is life-threatening for the individual taking part in the research, involves hospitalisation or an extended hospital stay, causes significant or permanent incapacity or disability, or leads to a congenital abnormality or malformation.

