## X - 3 - SERIOUS ADVERSE EVENT MANAGEMENT PROCEDURE

As this is a biomedical research study classified as “risk A”, i.e. for which there is a negligible **additional risk expected from the research**, no serious adverse events are expected through the course of the research.

Furthermore, there cannot be any suspected unexpected serious adverse reactions (SUSARs) related to the research.

In these conditions:

- The investigator will not be expected to declare any serious adverse events occurring during the research to the sponsor. Should such events occur, these will be related to the patient’s condition or their therapeutic treatment in the context of care, and will not be related to the research.

- It is not considered necessary to include a serious adverse event reporting form or an adverse event classification table with the protocol.

- It is not considered necessary to create an independent monitoring committee.

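### Section X-1 uses the term adverse event for two entries of different scope, and X-3 settles the causality of serious events in advance; both need aligning with X-2 and IX-1-7

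*Protocol*

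**What the plan says.** **X-1, first entry.** An adverse event is any harmful manifestation in a participant, "regardless of whether or not the manifestation is related to the research".

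**X-1, second entry.** Under the heading "Adverse event in a research study not involving a product mentioned in Article L. 5311-1", the definition is "Any adverse event due to the research".

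**X-1, seriousness.** The next definition begins "Any adverse event or effect that leads to death". The word *effect* appears here as a second term, but no entry defines it.

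**VII-2 and VII-3.** Spa physicians report adverse and serious adverse events that occur during the therapy. The list for Months 3, 6 and 12 has the item "Adverse events collected", with no limit by arm or cause.

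**IX-1-7.** Events are described per treatment group "according to their intensity and imputability to the treatment". Then: "The proportion of subjects with at least one adverse event will be compared between the groups", by the Chi-squared or Fisher's exact test. The section does not say which X-1 entry it uses.

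**X-2.** Among the main events linked to the exercise programme are increased pain, musculoskeletal injury, and decompensation of an arterial or cardiac condition during exercise.

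**X-3.** No serious adverse events are expected. Any that occur are attributed to the patient's condition or ordinary care "and will not be related to the research".

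**The concern.** There are two linked problems.

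**One term, two scopes.** The trial tests spa sessions, exercise and group education, so the second X-1 heading appears to describe it, although the protocol never says so outright. A site looking for the definition that fits its own study would land on the narrow entry. Control patients receive usual care, a back guide, questionnaires and pain calls, so few of their events would be judged due to the research. The adverse event proportions in the two arms would then differ largely because of what was counted. If some sites used one entry and some the other, rates would not be comparable between sites either. An event that is never recorded cannot be recovered by a later analysis plan.

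**Causality fixed beforehand.** X-2 names a harm of the exercise programme that could meet the X-1 criteria for seriousness, for example through hospitalisation or threat to life. X-3 rules that no serious event will be related to the research. If X-3 is followed, the imputability grading in IX-1-7 has little left to decide for serious events.

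IX-1-7 holds the only between-arm safety comparison that the protocol plans.

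**Working it through.** **Step 1. Scope of the two entries.** Let A be all harmful manifestations (first entry) and R those due to the research (second entry). The second entry takes the term adverse event from the first and restricts it, so R is a subset of A. Read as a replacement definition it would be circular; read as the definition of an adverse effect it makes sense. The pair of terms in the seriousness definition, with *effect* otherwise undefined, supports that reading.

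**Step 2. Which scope the rest of the protocol uses.**

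| Section | Content | Points to |
|---|---|---|
| General outline (visit table), VII-3 | Collection at Months 3, 6 and 12, no filter by cause or arm | Broad |
| VII-2 | Spa physicians report events during therapy, no causality filter | Broad |
| IX-1-7 | Imputability graded after collection, per group | Broad |
| X-3 | Calls events serious adverse events while declaring them unrelated | Broad |
| X-1, heading of second entry | Type of study that appears to match this trial | Narrow |

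The intent is broad. No sentence tells sites so, and the collection sections take over whichever meaning the reader found in X-1.

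**Step 3. X-3 against X-2 and IX-1-7.** X-2 allows an exercise-related event that could be serious. III-4 says the short spa programme is not offered outside this study, so an event caused by its exercises is hard to assign to ordinary care. X-3 nevertheless gives every serious event that attribution. The three sections cannot all be followed. Combined with the narrow X-1 entry, X-3 would leave no serious event that counts as an adverse event.

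**Step 4. Illustration of size.** The protocol gives no adverse event rate, so there is no planned figure to reproduce. Input from the Summary: n = 350 per arm. Assumptions: background proportion b in both arms; additional research-caused proportion r in the spa arm only; no research-caused event in controls.

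- Broad: spa count = n × [1 − (1 − b)(1 − r)], control count = n × b; Chi-squared test without continuity correction.
- Narrow: spa count = n × r, control count = 0; Fisher's exact test, two-sided.

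Example with b = 5%, r = 2%: 350 × [1 − 0.95 × 0.98] = 24.15, rounded to 24; 350 × 0.05 = 17.5, rounded to 18; 350 × 0.02 = 7.

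| r | b | Broad, spa v control | p | Narrow, spa v control | p |
|---|---|---|---|---|---|
| 2% | 5% | 24 v 18 | 0.34 | 7 v 0 | 0.015 |
| 2% | 30% | 110 v 105 | 0.68 | 7 v 0 | 0.015 |
| 5% | 5% | 34 v 18 | 0.02 | 18 v 0 | <0.001 |
| 5% | 30% | 117 v 105 | 0.33 | 18 v 0 | <0.001 |

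In three of these four rows the two definitions fall on opposite sides of 5%; with r = 5% and b = 5% they agree.

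**Step 5. Sensitivity at small counts (Fisher's exact, 350 per arm).** 5 v 0 gives p = 0.062 and 6 v 0 gives p = 0.031. Six excess spa events on top of one, two or three background events per arm give 7 v 1 (p = 0.069), 8 v 2 (p = 0.107) and 9 v 3 (p = 0.143). A little background moves the result only just past the threshold.

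**The case against.** The strongest reply is that this is a labelling slip whose intended reading is plain. Collection is not filtered by cause, imputability is sorted afterwards, and X-3 itself applies the term to unrelated events. Follow-up events come from patients by post, email or telephone, and patients do not choose between X-1 entries. The document shows no step at which a site discards events by cause. This largely stands: it establishes the intent, and it makes a split between sites a possibility and not a prediction. It does not supply the missing instruction on which entry governs.

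A reader might infer that the two definitions are incompatible, or that the narrow one makes the control count zero by definition. Neither is supported. The second entry is a subset of the first. Its wording ties events to the research and not to the spa therapy, and control patients also undergo research procedures: enrolment in the cohort, questionnaires, and fortnightly pain calls for a year. A control count near zero would be likely under the narrow reading, but the text does not fix it.

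A reader might also infer that any equal background rate would make a small spa excess far from significant. The 7 v 1 result shows that this is too strong.

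On X-3, the reply is that it speaks of relation to the research, whereas IX-1-7 grades imputability to the treatment, and that non-serious events are untouched. The second part stands: increased pain and other non-serious exercise effects can still be graded, so X-3 does not block detection of all the harms in X-2. The first part helps little, because the spa programme is the experimental treatment and is available only within the study.

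**Conclusion.** The point holds as a defect of wording with a possible effect on the safety data; it does not show that the safety comparison has failed. X-1 gives one term two scopes, the narrower under the heading that appears to fit this trial, and IX-1-7 does not say which applies. The document as a whole favours the broad sense, so harm arises only if sites follow the narrow entry as written. In that case the between-arm comparison would largely reflect the definition.

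The X-3 conflict does not depend on how X-1 is read. A causality statement made in advance for all serious events contradicts a harm that X-2 names and leaves the IX-1-7 grading little to decide for those events.

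The p-values are illustrations only. They rest on assumed background rates of 5% to 30%, assumed research-caused rates of 2% and 5%, and an assumed control count of zero under the narrow reading. None of these figures comes from the protocol.

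**What to change.** 1. In X-1, relabel the second entry as *adverse effect*.
2. State in X-1 and IX-1-7 that the first definition governs both collection and the compared proportions, identically in both arms, and that events judged related are described separately.
3. Reconcile X-3 with X-2 and IX-1-7 by removing the sentence that settles the cause of serious events in advance, so that their imputability is graded case by case as IX-1-7 already provides.

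The cost is one heading and a few sentences. The downside is that slightly more events may be recorded. The change helps most if made before sites begin to record events, since the analysis cannot restore events that were left out.

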**Serious adverse event or effect**

Any adverse event or effect that leads to death, is life-threatening for the individual taking part in the research, involves hospitalisation or an extended hospital stay, causes significant or permanent incapacity or disability, or leads to a congenital abnormality or malformation.

